Insomnia Severity Index		●		●		●		●		●	●
Patient Health Questionnaire 15		●				●				●	●
Patient Health Questionnaire 9		●		●		●		●		●	●
Generalized Anxiety Disorder 7		●		●		●		●		●	●
Weight (in kilograms)	●	●				●				●	●
Adverse Events Log		●	●	●	●	●	●	●	●	●	●
Electrocardiogram	●			●		●					
TSQM-side-effects item			●	●	●	●	●	●	●	●	●
Proportion completing dose escalation phase						●					
Secondary Outcomes											
Substance Use TLFB-MA (Days Used)	●	●	●	●	●	●	●	●	●	●	●
Urine Drug Screen (positive MA)	●^d^	●	●	●	●	●	●	●	●	●	●
Substance Use TLFB-MA (Days Used)		●	●	●	●	●	●	●	●	●	●
Urine Drug Screen^c^	●^d^	●	●	●	●	●	●	●	●	●	●
TSQM-effectiveness item		●	●	●	●	●	●	●	●	●	●
Visual Analogue Scale for MA craving		●^t^	●^t^	●^t^	●^t^	●^t^	●	●	●	●	●
Amphetamine Withdrawal Questionnaire		●^t^	●^t^	●^t^	●^t^	●^t^	●	●	●	●	●
Severity of Dependence Scale		●								●	●
Adapted Opiate Treatment Index (HIV & crime scales)		●				●					●
TSQM-convenience & global satisfaction items		●	●	●	●	●	●	●	●	●	●
Proportion discontinuing once enrolled			●	●	●	●	●	●	●	●	
Price would Pay		●^b^	●^b^	●^b^	●^b^	●^b^					
Similarity to MA Visual Analogue Scale		●^b^	●^b^	●^b^	●^b^	●^b^					
Drug Effects Questionnaire 5		●^b^	●^b^	●^b^	●^b^	●^b^					
Acute Subjective Response to Substances		●^b^	●^b^	●^b^	●^b^	●^b^					
Trail-making Test		●^t^	●^t^	●^t^	●^t^	●^t^					●
Rey Auditory Verbal Learning Task		●^t^	●^t^	●^t^	●^t^	●^t^					●
Digit-span sequencing		●^t^	●^t^	●^t^	●^t^	●^t^					●
Flankers Test with no-go		●		●		●					●
Digit Symbol Substitution		●		●		●					●
Rapid Information Processing		●		●		●					●

*Abbreviations*: ^*t*^timed trough/peak measurements prior to study drug administration/4 h post, *TSQM* Treatment Satisfaction Questionnaire for Medications, *MOCA* Montreal Cognitive Assessment, *AUDIT* Alcohol Use Disorder Identification Test, *WTAR* Wechsler Test of Adult Reading, *MA* methamphetamine, *TLFB* Time-Line Follow Back questionnaire

^a^vital signs measured daily

^b^Measurement taken 4 h post study drug administration

^c^Urine drug screen for benzodiazepines, cannabis, cocaine, methadone, morphine/heroin and oxycodone

^d^Two urines positive for methamphetamine required for eligibility

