Neuropsychological measures taken at baseline are the Montreal Cognitive Assessment (MoCA) [46] and the Wechsler Test of Adult Reading (WTAR) [47]. The Wender Utah scale is used to screen for the presence of co-existing Attention-Deficit Hyperactivity Disorder [48]. Two separate batteries of neurocognitive testing, Set A and Set B, are administered according to the schedule set out in Table 1, which also outlines the neurocognitive domains measured by each instrument. Neurocognitive Set A is paper based, and consists of the Rey Auditory Verbal Learning Task [49], Trail-making test [50, 51], and Digit-Span Sequencing [52]. Neurocognitive Set B is administered using an electronic tablet device, and consists of Flankers task [53], Digit Symbol coding [54] and Rapid Visual Information Processing task [54].

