#### Statistical analysis

Given the exploratory nature of the study, twenty participants will provide sufficient proof of the safety of the dose. While not powered to detect statistically significant effect sizes, findings will inform a planned randomised control trial of LDX for the treatment of methamphetamine dependence.

Descriptive statistics of proportion commenced on study drug who complete the study; proportion who achieve each dose; proportion who experience adverse event by type, severity and dose. Tolerability of LDX will be described using medians and interquartile ranges of TSQM side-effects scores. Continuous and categorical primary outcomes will be examined within a generalised linear mixed model framework [55]. Secondary outcomes measures changes in MA use, other substance use, craving, withdrawal, severity of dependence, risk behaviour scores and neurocognition will be tested for statistical significance using Wilcoxon rank-sum test for non-parametric data. The estimation of magnitude of effects of LDX on MA use will be calculated separately for those individuals that have and have not been adherent to counselling during the course of the study. Dose adequacy, medication acceptability, and potential for non-prescription use will be described using median scores and interquartile ranges at each dose. Analysis of urine drug results will follow established practice so that missing urine results are assigned as being positive for methamphetamine and the proportion of urines positive for methamphetamine will be reported. Missing data will be imputed using multiple imputation procedures.

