## Discussion

Research related to pharmacotherapy options for the treatment of methamphetamine dependence has been often underpowered, with some concerns of under-dosing also noted [6]. The publication of study protocols such as this not only represents good clinical trial practice, but allows for the sharing of methodology in phase 2 studies in addiction pharmacotherapy research. Safety data for this population are essential to ensure dosing at optimal levels in larger scale trials. As abstinence from methamphetamine use for the period of the trial is not mandatory, the safety data elicited from this trial may be applied to more “real-world” scenarios, such as outpatient programs for stimulant users. Limitations of the study include the lack of a control group and the small sample size. While this is typical of numbers required for safety data, it limits the generalizability of the secondary efficacy measures. The trial is open-label, and non-randomised and thus participants may be subject to expectancy effects. To mitigate this, subjects and dispensing nurses are aware of the minimum and maximum doses, but blinded to the dose and to the escalation and de-escalation regimen. Though concurrent methamphetamine use is dependent on self-report, a validated tool (the TLFB interview) is used to obtain this data. Determining the safety and dose optimization of LDX within the target population will provide valuable data for phase 3 studies on the efficacy of LDX to treat methamphetamine dependence.

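### With Set A cognitive tests given 10 to 11 times and no control group, the planned significance test of change in neurocognition cannot separate an LDX effect from practice

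*Protocol article*

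**What the plan says.** The Statistical analysis section of the protocol article puts cognition on the list of secondary outcomes to be tested: "risk behaviour scores and neurocognition will be tested for statistical significance using Wilcoxon rank-sum test for non-parametric data". By contrast, dose adequacy, acceptability and potential for non-prescription use are only described, with medians and interquartile ranges.

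On the schedule, the Secondary objectives section says "Two separate batteries of neurocognitive testing, Set A and Set B, are administered according to the schedule set out in Table 1". Set A "consists of the Rey Auditory Verbal Learning Task [49], Trail-making test [50, 51], and Digit-Span Sequencing [52"; Set B is three tablet tests. In Table 1 each Set A row carries the superscript t at five visits (columns -1, 1, 2, 3 and 4) and a plain mark at week 12. The footnote explains the superscript as "timed trough/peak measurements prior to study drug administration/4 h post". The Set B rows, such as "Flankers Test with no-go", have plain marks at columns -1, 2, 4 and 12.

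The Design section describes one group, with everyone stepping up weekly from 100 to 250 mg and then down. The Discussion states: "Limitations of the study include the lack of a control group and the small sample size". It ties these limitations to the generalizability of the secondary efficacy measures, and ties the open, non-randomised design to expectancy effects. Practice is not mentioned.

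**The concern.** People usually do better on word-list learning, trail making and similar timed tasks when they repeat them, whether or not they take a drug. Without a control group, only the study's own schedule could separate practice from drug, and this schedule does not. All on-drug cognitive testing falls between the first dose and the maximum dose. A later session therefore means at least as high a dose and also more practice. Within a day, the peak test is always the second one, four hours after the trough test. The descending weeks would have paired more practice with less drug, but they have no cognitive testing.

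Two misreadings are possible. A practice gain could be reported as a cognitive benefit of high-dose LDX, or practice could hide a real decline. The second matters in a study whose purpose is safety. The article says that the findings will inform a planned randomised trial, so either error could carry forward. A larger sample would not help, because this is confounding and not imprecision.

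**Working it through.** **1. Number of administrations (Table 1).** A cell marked t counts as two (trough and peak), a plain cell as one.

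- Set A: 5 × 2 + 1 = 11.
- Set A if the first visit is a single pre-dose session: 1 + 4 × 2 + 1 = 10.
- Set B: 4.

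The first figure is uncertain because Table 1 and the text do not line up. The table's dose row puts 100 mg under week -1, whereas the Design section starts dosing in week 1, and the Assessment schedule section places one extended visit per week in weeks 1-4. These places need to be reconciled.

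**2. Is dose tied to session number?** By the Design text, the weeks 1 to 4 sessions fall at 100, 150, 200 and 250 mg. By the table's dose row, the five timed visits fall at 100, 150, 200, 250 and 250 mg. On either reading dose never falls as sessions accumulate, and no session falls in the descending weeks.

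**3. Effect on the planned test.** The plan states no figure to reproduce: it gives 20 participants and no alpha, power, effect size or SD. The practice gain and retest correlation below are therefore assumptions. The model is bivariate normal baseline and retest scores, unit SD, zero drug effect, retest mean shifted by the practice gain, two-sided 0.05 and 4,000 simulated trials per setting. The table gives the proportion significant with n = 20, each range running over correlations 0.6, 0.7 and 0.8.

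| Assumed gain (SD) | Rank-sum, as written | Signed-rank, paired |
|---|---|---|
| 0 | 0.000-0.003 | 0.044-0.051 |
| 0.2 | 0.007-0.026 | 0.154-0.261 |
| 0.3 | 0.027-0.066 | 0.296-0.500 |
| 0.5 | 0.226-0.255 | 0.642-0.904 |
| 0.8 | 0.751-0.818 | 0.959-0.999 |

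Separate runs differ by a percentage point or two, so the rounded ranges used elsewhere in this point are slightly wider.

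With 14 participants the paired rates are lower: 0.116-0.186 at 0.2 SD, 0.212-0.374 at 0.3 SD and 0.482-0.748 at 0.5 SD.

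**4. Why the two tests differ.** The rank-sum test treats the two sessions as independent groups. The real standard deviation of the difference is √(1 − ρ) times what the test assumes: √0.4 = 0.63 at ρ = 0.6 and √0.2 = 0.45 at ρ = 0.8. The effective critical value is thus about 1.96 / 0.63 = 3.1 or 1.96 / 0.45 = 4.4, which explains the near-zero rate when there is no gain. The low rates come from ignoring the pairing, not from any handling of practice.

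**5. What two contrasts can show.** Orient scores so that higher is better. Let D be the drug effect at an on-drug session, P the practice gained by then, and P12 the practice gained by week 12.

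- On-drug minus baseline = D + P.
- On-drug minus week 12 = D − (P12 − P).

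If 0 ≤ P ≤ P12, the first is at or above D and the second at or below it, so D lies between them. For illustration, D = 0, P = 0.3 and P12 = 0.5 give +0.3 and −0.2. The signs disagree, and no drug effect would be claimed.

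**The case against.** The strongest reply is that the plan names the rank-sum test, and with that test small practice gains are not declared significant more often than about the nominal 5%: 0-3% at 0.2 SD and 3-7% at 0.3 SD. This stands. A reader might infer that the test as written is badly anti-conservative, but the material shows that only for larger assumed gains. The protection is accidental, though. It disappears if the pairing is respected, and it leaves the bias in the estimated change untouched.

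A second reply is that rejecting no change is correct if scores really rise through repetition. This also stands. The hypothesis test is not false in itself; what fails is attribution to LDX. The article makes no such attribution for cognition, so the claim that the trial will report a spurious benefit is a prediction that the documents do not support.

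Third, the study is exploratory, is described as not powered, and admits that it lacks a control. That lowers the stakes but does not answer the point. The caveat concerns generalizability and expectancy, and blinding to dose does nothing about practice.

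Fourth, alternate forms or familiarisation sessions may be in the full protocol, which is not shown, so their absence here is no finding. Alternate forms would reduce item memory, but they would not break the link between dose and test order.

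Finally, using week 12 as the sole comparator would create the opposite bias. Week 12 carries the most practice, so with no drug effect the on-drug visits would look impaired. This objection is right, and the fix allows for it.

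**Conclusion.** The point holds in a limited form. As scheduled, the planned significance test of change in neurocognition cannot distinguish an LDX effect from practice, and the stated limitations do not cover this. The conclusion rests on three things that the article fixes: a single group, one dose order for everyone with cognitive testing only on the way up to the maximum, and a commitment to significance-test change.

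The size is conditional. For assumed gains of 0.2, 0.3 and 0.5 SD with n = 20, correlation 0.6 to 0.8 and no drug effect, significance occurs in about 0-3%, 3-7% and 22-27% of trials with the test as written, and in about 15-26%, 28-50% and 64-91% with a properly paired test. The documents do not say how large practice gains are, or which sessions are to be compared. The heavy repetition applies only to the three Set A tests; Set B is given four times. This is a secondary outcome in a safety study, so the point bears on what may be concluded about cognition and not on the primary objectives.

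**What to change.** Do not use the significance test of cognitive change as evidence of an LDX effect. Instead:

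- Report paired median change with a 95% CI by session, labelled as drug plus practice.
- Show each on-drug session against two references: the pre-dose baseline, where practice favours the on-drug visit, and the already scheduled off-drug week-12 session, where practice favours week 12.
- Draw a cognitive conclusion only where both contrasts agree in direction, read with their intervals.
- Describe the same-day peak-minus-trough difference without inference, since order and drug are inseparable there.
- Reconcile Table 1 with the text on whether the first timed visit is before any dose, so that the baseline session is unambiguous.

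The cost is analysis wording; no assessment is added. The downside is that the week-12 contrast covers only those who return, and it may be affected by practice decay, drug cessation and ongoing methamphetamine use. If practice has decayed by week 12 below its level at the on-drug session, the two contrasts no longer bracket the drug effect. Week 12 is therefore a supporting bound and not a sole comparator.

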**Methods/design:**

This is a phase 2 dose escalation study of lisdexamfetamine for the treatment of methamphetamine dependence. Twenty individuals seeking treatment for methamphetamine dependence will be recruited at two Australian drug and alcohol services. All participants will undergo a single-blinded ascending-descending dose regime of 100 to 250 mg lisdexamfetamine, dispensed daily on site, over an 8-week period. Participants will be offered counselling as standard care. For the primary objectives the outcome variables will be adverse events monitoring, drug tolerability and regimen completion. Secondary outcomes will be changes in methamphetamine use, craving, withdrawal, severity of dependence, risk behaviour and other substance use. Medication acceptability, potential for non-prescription use, adherence and changes in neurocognition will also be measured.

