## Methods

### Design

The study is a phase 2, single group, outpatient study with a study period of 14 weeks, inclusive of screening and follow up. Screening will occur over 2 weeks (weeks −2 and −1), and eligible participants commenced on the escalation/de-escalation phase (week 1). Escalation of LDX will occur over 4 weeks, beginning at 100 mg/day, with weekly increases of 50 mg to a maximum 250 mg/day. After 2 weeks at 250 mg/day LDX, the dose of LDX will be reduced weekly by 50 mg/day, ceasing after 1 week at 100 mg/day. A follow up study visit will occur in week 12, 4 weeks after cessation of study drug. The study aims to enrol a sample of twenty participants who are seeking treatment for methamphetamine dependence. A diagrammatic overview of the study is given in Fig. 1. The protocol has been designed in accordance with CONSORT SPIRIT guidelines [27].

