### Study objectives

The study’s primary objectives are to describe the safety, tolerability and regimen completion of ascending doses of LDX in adults with methamphetamine dependence.

Secondary outcomes include changes in methamphetamine use, craving, withdrawal, severity of dependence, risk behaviour and in other substance use. Medication acceptability, potential for non-prescription use, adherence and changes in neurocognition will also be measured.

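### Changes in seven secondary outcomes of a single-group study are to be tested with the Wilcoxon rank-sum test, which needs two independent samples; a paired test is required

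*Protocol article*

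**What the plan says.** The Statistical analysis section of the protocol article covers "Secondary outcomes measures changes in MA use, other substance use, craving, withdrawal, severity of dependence, risk behaviour scores and neurocognition" and states that these "will be tested for statistical significance using Wilcoxon rank-sum test for non-parametric data". The signed-rank test is not mentioned anywhere in the article.

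The design is described consistently. Under Design: "The study is a phase 2, single group, outpatient study". In the abstract: "All participants will undergo a single-blinded ascending-descending dose regime of 100 to 250 mg lisdexamfetamine". In the Discussion: "Limitations of the study include the lack of a control group and the small sample size". The planned sample is twenty participants (Design). Study objectives defines the outcomes concerned as changes: "Secondary outcomes include changes in methamphetamine use, craving, withdrawal, severity of dependence, risk behaviour and in other substance use". Table 1 shows them measured on several occasions in the same people.

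For continuous and categorical primary outcomes, the same section plans a generalised linear mixed model. It also states that the study is exploratory and not powered for significance testing, and that its findings are to inform a later randomised trial.

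**The concern.** The rank-sum (Mann–Whitney) test asks whether two independent samples come from the same distribution. A change over time in one group gives two sets of values from the same people, or equivalently one set of differences. It does not give two independent samples. An analyst who follows the text literally would have to treat baseline and later values as if they came from different participants. The test would then use a standard error that is too large whenever a person's values are positively correlated over time, which is the usual case for repeated measures.

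What is at stake is a real change in use, craving or withdrawal being reported as non-significant in a sample of twenty, when these findings are meant to guide the design of a randomised trial.

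**Working it through.** **Step 1. Is there a second group for the test?**

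- Treatment arms: none. There is a single group without controls (Design; Discussion).
- Dose groups: none between persons. Everyone follows the same ascending-descending regimen, so dose varies within person.
- Counselling adherence: this is the only between-person split in the section. The plan there is to estimate the effect on methamphetamine use separately in the two subgroups. No test between them is stated, and the other six outcomes are not included.

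No reading of the text supplies two independent samples for the listed outcomes.

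**Step 2. Which way does the error go?** The article gives no alpha, power or correlation, so there is no planned figure to reproduce. Let each measurement have SD σ, with within-person correlation ρ and n pairs. The variance of the difference in means is

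- as the two-sample test assumes: 2σ²/n
- in fact: 2σ²(1 − ρ)/n

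A nominal 1.96 cut-off therefore acts as 1.96/√(1 − ρ). As a large-sample approximation that treats ranks like means:

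- ρ = 0.3: 1.96/0.837 = 2.34, two-sided error about 0.019
- ρ = 0.5: 1.96/0.707 = 2.77, about 0.006
- ρ = 0.7: 1.96/0.548 = 3.58, about 0.0004

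Positive correlation makes the test conservative.

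**Step 3. Simulation at the trial's size.** Inputs: n = 20 pairs (the planned enrolment). Assumed: bivariate normal data with SD 1, two-sided alpha 0.05, and the correlations and shifts shown. There were 20,000 runs per setting. Rank-sum (asymptotic) treats the two time points as independent samples; signed-rank (exact) uses the paired differences.

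| ρ | Type I error, rank-sum | Type I error, signed-rank | Power at 0.5 SD, rank-sum | Power at 0.5 SD, signed-rank | Power at 0.7 SD, rank-sum | Power at 0.7 SD, signed-rank |
|---|---|---|---|---|---|---|
| −0.3 | 0.085 | 0.049 | 0.34 | 0.25 | 0.55 | 0.44 |
| 0 | 0.050 | 0.050 | 0.32 | 0.31 | 0.56 | 0.53 |
| 0.3 | 0.023 | 0.048 | 0.29 | 0.41 | 0.57 | 0.69 |
| 0.5 | 0.009 | 0.046 | 0.28 | 0.54 | 0.57 | 0.82 |
| 0.7 | 0.001 | 0.046 | 0.24 | 0.76 | 0.61 | 0.96 |

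A separate simulation with 6,000 runs per setting gave rank-sum errors of 0.022, 0.009 and 0.002 at ρ = 0.3, 0.5 and 0.7. At this sample size the simulated errors are somewhat above the approximation in Step 2 but follow the same pattern.

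**Step 4. Fewer pairs.** With 14 pairs and a 0.5 SD change, power at ρ = 0.3, 0.5 and 0.7 is 0.19, 0.16 and 0.13 for rank-sum, against 0.30, 0.40 and 0.59 for signed-rank.

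**The case against.** The best defence is that this is a slip of name: in a single group, a Wilcoxon test of change can sensibly mean only the signed-rank test. If the analyst runs that test, none of the loss above occurs. That is plausible, but the text names a specific and different test, so it still needs correcting.

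The second defence is that the study is exploratory and disclaims power, and that its primary objectives (safety, tolerability and regimen completion) do not use this test. This stands and limits the severity. It does not remove the point, because the plan still commits to significance tests on these outcomes.

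A reader might also infer four stronger things that the article does not support:

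- **That the secondary p-values would be falsely significant.** Under positive correlation they are too large. In the simulation the error exceeds 0.05 only with negative correlation (0.085 at −0.3).
- **That dropout would turn a change in who attends into an apparent change in outcome.** The section plans multiple imputation and counts missing urine results as positive. Without imputation, a signed-rank test on completers would be exposed to selective dropout too.
- **That only two time points would be used.** No time points or contrasts are stated, and an article may leave that detail to the full plan.
- **That every secondary outcome is affected.** Dose adequacy, acceptability and potential for non-prescription use are only described, by medians and interquartile ranges. For methamphetamine urines the text promises a reported proportion, and a test of it is not clearly intended.

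**Conclusion.** The test is wrong as written: a two-independent-sample test is named for within-person change in a trial with no second group. It affects the seven outcomes listed for that test and nothing else.

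If applied literally, the test is miscalibrated in the conservative direction. For correlations of 0.3 to 0.7, the type I error is about 0.02 down to 0.001–0.002 in place of 0.05. Power for a 0.5 SD change falls by 0.12 (0.41 − 0.29) at the low end and 0.52 (0.76 − 0.24) at the high end. These sizes rest on assumed correlations, shifts, normality, alpha and 20 complete pairs, none of which (apart from the enrolment of twenty) is in the article. That baseline is compared with a later visit is the natural reading but is not spelled out. At zero correlation the two tests perform about equally.

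Severity is moderate. The outcomes are secondary and exploratory, and the primary safety analyses are untouched.

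**What to change.** In the Statistical analysis section, replace the rank-sum test with the Wilcoxon signed-rank test on each participant's change from baseline, preferably reported with a Hodges–Lehmann estimate and 95% confidence interval. For any binary outcome that is tested, name a paired method such as McNemar's test.

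Optionally, extend the mixed model already planned for the primary outcomes to the secondary outcomes collected weekly, and keep signed-rank for those measured only a few times. This is a preference that makes fuller use of the data and is not needed to correct the error.

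The cost is one sentence. No new data, visits or participants are needed.

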### Intervention

The LDX dosing period is up to 8 weeks and consists of daily, supervised outpatient oral dose administration at the participants’ respective site. Dose escalation and de-escalation range from 100 mg per day to a maximum 250 mg per day, with changes weekly to allow for achievement of steady state [29]. Both the participants and drug administration personnel are blinded to date, amount and direction of dose change. To achieve this, the dose comprises 5 identical size 0 capsules each containing either 50 mg LDX or placebo according to the dose escalation phase.

Additionally, participants are offered weekly counselling with trained and supervised counsellors at the Stimulant Treatment Programs as current standard of care for methamphetamine dependence, though attendance is not mandatory.

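### Splitting the effect on methamphetamine use by counselling adherence during the study conditions on self-selected, post-baseline behaviour; for urine results, dropout can by itself create part of any difference

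*Protocol article*

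**What the plan says.** Under Statistical analysis, the protocol article announces "The estimation of magnitude of effects of LDX on MA use", to be "calculated separately for those individuals that have and have not been adherent to counselling during the course of the study". The Intervention section offers counselling weekly "as current standard of care for methamphetamine dependence, though attendance is not mandatory". Under Design, "The study is a phase 2, single group, outpatient study". The Statistical analysis section also states that "missing urine results are assigned as being positive for methamphetamine", and provides multiple imputation for missing data. Methamphetamine use is measured both by Timeline Follow-back and by urine (Secondary objectives). The article does not say which measure the split uses, nor how adherence is defined. The Safety and discontinuation section withdraws participants who miss enough doses or extended visits. The study is described as exploratory and "While not powered to detect statistically significant effect sizes", but its findings are meant to inform a planned randomised trial.

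**The concern.** Adherence over the course of the study is not a baseline characteristic. Participants choose it after dosing starts, and someone who is already using less may find it easier to attend. With no control arm, each subgroup effect is a before-after change, so anything that separates attenders from non-attenders appears as a difference in drug effect.

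For urine results, retention may also enter twice. A participant who leaves early has fewer sessions to attend, and the same departure turns later urines into positives. One event can then influence both the group and the outcome.

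At stake is a small table that seems to show lisdexamfetamine doing better when combined with counselling. That is a natural thing to carry into the design of the next trial. The Discussion names the missing control group, the small sample and expectancy as limitations, but says nothing about this split.

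**Working it through.** The plan gives no figure for this split, so there is nothing to reproduce. The check asks what the split would show if neither drug nor counselling had any effect.

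**Inputs from the article:** 20 participants; 8 weeks of dosing with weekly counselling offered; missing urine counted as positive; two methamphetamine-positive urines needed for eligibility (Table 1, note d).

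**Assumptions, not in the article:** weekly dropout *d* of 2–8%; attendance *a* of 50–70% per session while enrolled; adherent means at least 4 of all 8 sessions; true urine positivity *p* = 75%. Dropout, attendance and use are independent of each other.

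**Formulas.** Let *k* be the weeks completed.
- P(k) = d(1−d)^k for k = 0 to 7, and (1−d)^8 for k = 8.
- P(adherent given k) = P(Binomial(k, a) ≥ 4).
- Share of urines missing: m = (8−k)/8.
- Positivity in a group = p + (1−p) × mean m in that group.
- False gap = (1−p) × (mean m in non-adherent − mean m in adherent).

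**One case in full (d = 5%, a = 70%).** Mean m is 0.033 in the adherent and 0.618 in the non-adherent.
- Adherent: 0.75 + 0.25 × 0.033 = 75.8%.
- Non-adherent: 0.75 + 0.25 × 0.618 = 90.5%.
- Gap: 0.25 × 0.585 = 14.6 points. A simulation of 400,000 participants gave the same gap. Complete data would give 75% in both groups.

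**False gap over the range, in percentage points:**

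| Weekly dropout (lost by week 8) | Attendance 50% | 60% | 70% |
|---|---|---|---|
| 2% (15%) | 4.4 | 7.1 | 11.7 |
| 5% (34%) | 8.4 | 11.3 | 14.6 |
| 8% (49%) | 10.8 | 13.1 | 15.5 |

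Across these cells, 11–28% of dropouts are still classed as adherent. The gap scales with 1 − p, so at 60% positivity each entry is multiplied by 0.40/0.25 = 1.6. A separate simulation with 60% mean positivity and 60% mean attendance, cut-offs of 50% or 75% of sessions and 20–50% total dropout gave 7–18 points, with on average about 5–14 of 20 participants classed as adherent.

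**Sensitivity to the definition:**
- *Adherence counted only while in the study:* 2–7 points in the separate simulation. In the table's model it is smaller in every cell; for example 10.8 instead of 14.6 at 5% and 70%, if someone who leaves before any session counts as non-adherent.
- *Counselling continues after trial withdrawal:* about 0.
- *Observed urines only:* about 0 under every definition.
- *Week-4 landmark:* about 0, because later dropout is then unrelated to the grouping.

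**Levels and change.** Because entry requires positive urines, all participants start positive. A gap in on-study positivity therefore passes straight into a gap in change from baseline.

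**Selection without dropout.** As an illustration, let each person's urine positivity follow a Beta(3, 1) distribution (mean 75%), let attendance be 0.6 − 0.5 × (positivity − 0.75), and keep the cut-off at 4 of 8. With no dropout and no effect of anything, the groups differ by 14 points in fully observed urines. The size depends wholly on the assumed link and spread. The illustration shows only that using observed urines does not remove selection.

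**The case against.** A reader might infer that dropouts cannot be adherent, so that the split must create a difference. The article does not support that. It gives no definition of adherence, which may properly sit in an analysis plan not shown here, and its absence is no finding. Late dropouts can reach a cut-off, and counselling is standard care that may continue after trial withdrawal. This objection stands: the retention artefact depends on the definition.

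A reader might also take a single figure such as 15 points as the expected bias. Dropout, attendance and cut-off are all assumed, so only a range is defensible.

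The rule on missing urines is stated for urine results. Timeline Follow-back days fall under multiple imputation, and the check shows no artefact for them. This also stands.

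Finally, the article plans two separate estimates, with no test between them, and ties no phase 3 decision to the split. It is therefore not established that the trial would report a larger effect with counselling. The analysis is secondary and exploratory, and the primary safety, tolerability and completion objectives are untouched. That limits the weight of the point. It does not answer it: two estimates set side by side invite comparison, and self-selection affects either measure of use under any definition of adherence during the study.

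**Conclusion.** The point holds in a limited form. The split is on post-baseline, self-selected behaviour in a single-arm study, so a difference between the two estimates cannot be attributed to counselling changing the drug's effect. This part needs no numerical assumption.

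The retention artefact is conditional. It requires the urine outcome with missing counted as positive, and adherence that depends on staying in the study. Counted over all 8 sessions, with 2–8% weekly dropout, 50–70% attendance, a cut-off of 4 and 75% true positivity, it is about 4–16 points with no true effect. It shrinks or vanishes under the alternatives shown in the working. The change is worth making before analysis, but the primary conclusions do not depend on it.

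**What to change.** Make the whole-group change in methamphetamine use the main estimate. Then either drop the split or replace it with one of these:
- a landmark: classify attendance up to week 4 and describe use in weeks 5–8 among those still in the study, alongside baseline use; or
- the previous week's attendance as a covariate in a weekly model.

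In this comparison use observed urines, not missing counted as positive. Label the result a descriptive association, not an effect of lisdexamfetamine with or without counselling.

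The cost is wording, plus some participants: at 5% weekly dropout, 20 × 0.95^4 ≈ 16 would reach the landmark, in a comparison that is already small. Selection by motivation or early response remains, so the descriptive label is needed whichever version is used.
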